### 3.5. Survey Design 

Data from all secondary outcome measures will be recorded in an online survey management system: www.limesurvey.org [27]. Item wording and response options were composed to align with the Australian Bureau of Statistics (ABS) 2016 Census and the Australian Longitudinal Study on Women’s Health (ALSWH) to allow for comparison of outcomes [28,29]. Survey questions were generated using a developmental model [30] that employs five stages of questionnaire design and testing: conceptualization, design, testing, revision, and data collection. The feasibility study allowed testing of questions to ensure they were comprehendible, relevant and appropriate to participants and to confirm the survey length was suitable. Revisions were then made based on the feedback provided. For example, some participants in the feasibility study felt they were being asked the same question twice in the Healthy Eating Belief Scale. Therefore, the interviewer’s scripted introduction and description of the Healthy Eating Belief Scale was modified to notify participants that there would be some repetition. The second draft was then pilot tested on three adults outside of the research team to ensure comprehensibility, suitability and flow.

### 3.6. Outcome Measures 

Table 2 provides an overview of the primary (diet quality) and secondary outcomes and when they will be collected. 

#### 3.6.1. Primary Outcome Measure: Change in Diet Quality (measured by DASH score)

Diet quality can be measured by a variety of purpose developed tools [31]. These are constructed by assigning higher scores within sub-scales based on more frequent or higher intakes of foods, nutrients or both [31]. Dietary Approaches to Stop Hypertension (DASH) is a dietary pattern high in whole-grains, fruits, and vegetables; moderate in low-fat dairy; and low in red and processed meats, added sugars, and sodium [32]. While originally developed to assist people in the prevention and management of hypertension, DASH is now recommended for the dietary management of T2D [18,33]. Adherence to DASH positively impacts on glycemic control, weight, and hypertension, which are key indicators of risk for diabetes-related complications [5,18,32]. A randomized controlled trial (RCT) conducted in adults with T2D showed that adherence to DASH improved glycated hemoglobin (HbA1c) (−1.2%), fasting blood glucose (−0.92 mmol/L), weight (−3 kg) and waist circumference (−4.8 cm) over 8 weeks when compared with a control diet [34,35]. Those following the DASH dietary pattern, also had a greater reduction in LDL cholesterol (difference from the control diet, −7.7 ± 3.3%).

A systematic review and meta-analysis of 20 RCTs found DASH significantly reduced systolic (−5·2 mmHg) and diastolic blood pressure (−2·6 mmHg) in adults with and without diabetes [36]. Another systematic review and meta-analysis of 13 RCTs revealed that adults without T2D who adhered to DASH achieved greater weight loss (−1.42 kg), reduced Body Mass Index (BMI) (−0.42 kg/m^2^) and decreased waist circumference (−1.05 cm) compared with controls [37]. Considering the recognized impact on glycemic control, weight and hypertension, DASH was chosen as the dietary pattern used to assess diet quality in the present study. Participant DASH scores will be calculated using the DASH diet-quality tool which has been shown to have the highest correlation with health outcomes related to T2D compared to other tools that measure diet quality [38,39].

Change in DASH score from baseline to 3 months will be used to categorize participants as diet quality improvers or diet quality maintainers. Participants will be split into 2 groups; those who improved their DASH score by at least 3 DASH points (Diet quality improvers) and those who maintained their DASH score within 2.99 points or decreased their DASH score by at least 3 points (Diet quality maintainers). A change in DASH score of 3 points was selected based on findings from previous literature [40]. In a 20-year longitudinal study of over 40,000 adults, an average DASH score of 23.8 out of 40 was observed, and a change in score of approximately 3 points or more was sufficient to significantly influence long-term glycemic control [40]. 

Dietary intake data will be obtained through the Australian version of the Automated Self-Administered 24-h Dietary Assessment Tool (ASA-24). The ASA-24 is based on the validated Automated Multiple-Pass Method (AMPM) which is considered the optimal method for obtaining 24-h recall data due to its numerous probes, standardization of interviewer administration and validation against recovery biomarkers [41,42]. This method is also consistent with the methodology of the most recent population nutrition survey in Australia (the National Nutrition Survey) and has been shown to be a valid measure of dietary behavior at a given time point [43,44]. The ASA-24 is an online automated questionnaire that guides the individual through a system designed to maximize respondents’ opportunities for remembering and reporting foods eaten in the previous 24 h [45]. The questionnaire is divided into five phases in line with published methodological guidelines; ‘quick list’, ‘forgotten foods’, ‘time and occasion’, ‘detail cycle’, and ‘final probe’ [45]. These phases encourage respondents to think about their intake in different ways and from several perspectives which has been shown to reduce bias in the estimation of dietary intake [45]. Once a specific food or beverage is reported, systematic questions are asked to capture more precise information about the food, cooking methods and quantity consumed. The ASA-24, usually a self-completed tool, will be adapted for use in a telephone survey; a researcher will ask the questions and enter the data. This will reduce participant burden and help decrease any bias associated with participant information technology literacy levels. This process was carried out successfully in a feasibility study with patients newly diagnosed with T2D. The data from the feasibility study was able to be used to assess changes in diet quality over a 12-month period. 

Following data collection, participant 24-h dietary recall data will be sent from the ASA-24 program to the research team. This data will then be manually entered into FoodWorks by an experienced dietitian to allow determination of participant DASH scores. FoodWorks is a dietary analysis software program using standardized serve sizes that allows for quantification of specific food groups (e.g., vegetables) and nutrients (e.g., sodium) obtained from reported dietary intakes, recipes and meals [46]. FoodWorks draws on the national AUSNUT database [47]. AUSNUT was developed by Food Standards Australia and New Zealand and includes complete nutrient data sets of Australian foods designed specifically for nutrition surveys and is therefore suitable for use in this project [47]. 

DASH scores will be calculated using the standard scoring tool created by Fung et al [39]. Every tenth DASH score will be cross-checked by a second member of the research team to ensure accuracy. The standard scoring tool determines a score between 8 and 40 points, with 40 points representing optimal accordance with the DASH dietary pattern [39]. The DASH score is calculated by summing the number of daily servings of seven dietary components; fruits, vegetables, nuts and legumes, whole-grains, low-fat dairy, red and processed meats, added sugar, and sodium intake. For each of the components, participants are classified according to their intake ranking. Higher intakes of fruits, vegetables, low-fat dairy, whole-grains, and nuts and legumes receive higher scores. For example, quintile 1 is assigned 1 point and quintile 5 is assigned 5 points. Intake of sodium, red and processed meats and added sugars are scored in reverse as these are less desirable foods [39]. The lowest quintile is given a score of 5 points and the highest quintile is given a score of 1 point. The components scores are then summed to give an overall DASH score [39]. The scoring criteria for the DASH-style diet is outlined in Table 3.

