### 3.8. Statistical Modeling and Sample Size 

The longitudinal aspect of diet quality change will be analyzed using regression models [74]. Diet quality at 12 months (measured by the DASH score) will be the primary outcome, with glycemic control, interim diet changes (primarily at 3 months), medication use, demographic measures, physical measures, psychosocial measures, and exposure to healthcare provider support as the explanatory variables. This model will determine the relative importance of diet quality change both immediately after diagnosis and in the medium term with regards to a 12-month outcome towards sustained healthy eating. 

Sample size calculations, such as those provided in Diggle et al. [74] are not readily computed for complex regression models and assessment using simulation studies would be more appropriate [75]. However, due to the relatively small participation rate in the feasibility study (22 participants/1000 invited) credible model parameters are currently unable to be formulated, and the effect differences over time cannot be reliably inferred. Additionally, current research of diet quality change post diabetes is lacking [15], therefore effects cannot be competently elicited. As a result, rather than determining an initial sample size for the study, a Bayesian updating procedure will be used to collect data. In this manner, sample size will be calculated during the early stages of data collection to yield an idea of how many samples should be collected. Additionally, using a Bayesian framework, the parameter estimates of the mixed model will be sequentially updated as batches of data are obtained, a process known as Bayesian learning [76,77]. 

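### The 3-month DASH change is cut at +3 into two groups; wherever those groups are used for inference, at least about a third of the information is likely to be lost, and section 3.8 does not say which form it uses

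*Protocol article*

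**What the plan says.** Section 3.6.1, under the heading "Primary Outcome Measure: Change in Diet Quality (measured by DASH score"), states the rule: "Change in DASH score from baseline to 3 months will be used to categorize participants as diet quality improvers or diet quality maintainers". It then defines the upper group: "Participants will be split into 2 groups; those who improved their DASH score by at least 3 DASH points (Diet quality improvers"). The lower group is "those who maintained their DASH score within 2.99 points or decreased their DASH score by at least 3 points (Diet quality maintainers"), so it pools no material change with worsening. The reason given is that "A change in DASH score of 3 points was selected based on findings from previous literature [40"], a 20-year cohort in which a change of roughly this size was reported to matter for long-term glycemic control. On the scale, the section says: "The standard scoring tool determines a score between 8 and 40 points".

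Section 3.8 makes the 12-month DASH score the primary outcome and does not cut it. Its explanatory variables include "interim diet changes (primarily at 3 months), medication use" and others. It does not say whether the 3-month change enters as the two groups or as a number of points. It fixes no sample size and plans Bayesian updating as batches of data arrive.

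**The concern.** A change score on an 8-to-40 scale is reduced to yes or no. A gain of 3 and a gain of 12 count the same, while gains of 2 and 3 fall on opposite sides. A person who drops 10 points carries the same label as one who does not move, although the introduction asks whether diet quality shows marked increases or decreases after diagnosis.

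The grouping is stated under the primary outcome heading and is the only form given for the 3-month change, so an analyst could reasonably carry it into the section 3.8 model or into an analysis of who improves (aim ii). Real associations would then be estimated less precisely. The study has little to spare: in the feasibility work (section 3.3), 22 of 1000 invitees were recruited, 17 completed baseline and six had left by 3 months. This loss is separate from recall error and would remain if the change were measured perfectly.

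**Working it through.** **Inputs from the protocol article.** Cut at +3; score range 8 to 40; whole-number scores, because Table 3 gives each of eight components 1 to 5 points. The article states no power, alpha or sample size, so it has no figure of its own to reproduce.

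**Inputs assumed, because the article does not give them.** The 3-month change is near normal, with mean 0 to 3 and SD 3 to 7. Its relation to the other variable is linear. Tests are two-sided at 0.05, with 80% reference power for the analysis that keeps the score.

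**Step 1: relative efficiency.** Let p be the share of improvers and c the standard normal cut-point with upper tail p. The efficiency of the two-group variable relative to the score is E = φ(c)² / [p(1 − p)].

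- p = 0.50: φ(0) = 0.399, so E = 0.159 / 0.25 = 0.637. Loss = 36.3%.
- p = 0.26: c = 0.643, φ(c) = 0.324, so E = 0.105 / 0.192 = 0.547. Loss = 45.3%.

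E is largest at p = 0.50, so 36% is a floor under these assumptions. It is symmetric about one half, so 74% improvers gives the same loss as 26%.

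**Step 2: power.** Power with groups = Φ[(1.960 + 0.842) × √E − 1.960].

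- p = 0.50: 2.802 × 0.798 − 1.960 = 0.275, so power = 60.8%.
- p = 0.26: 2.802 × 0.740 − 1.960 = 0.112, so power = 54.5%.

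| Improvers | E | Information lost | Participants needed (1/E) | Power, from 80% |
|---|---|---|---|---|
| 50% | 0.637 | 36.3% | 1.57 times | 60.8% |
| 40% | 0.622 | 37.8% | 1.61 times | 59.8% |
| 30% | 0.576 | 42.4% | 1.74 times | 56.6% |
| 26% | 0.547 | 45.3% | 1.83 times | 54.5% |
| 20% | 0.490 | 51.0% | 2.04 times | 50.0% |
| 10% | 0.342 | 65.8% | 2.92 times | 37.4% |

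**Step 3: range over the assumptions.** With SD 3 to 7 and mean change 0 to 3, and the cut placed at 3 or at 2.5 to allow for whole-number scores, improvers are 16% to 57%, the loss is 36% to 56%, and the drop from 80% power is 19 to 34 points. The worst cases have a small SD and no mean change. The drop also depends on the reference power. For p from 0.50 to 0.26 it is 15 to 20 points from 50%, 17 to 23 from 90%, and 6 to 10 from 99%.

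**Step 4: simulation.** With whole-number change scores, 100 or 200 participants and a linear effect, the drop was 18 to 24 points at SD 4 to 5, and about 31 points at SD 3 with mean 0. This agrees with the formula.

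**Step 5: the case in which the groups win.** When the simulated outcome depended only on being at or above +3 (SD 5, mean 1 or 2, 200 participants), the groups had about 80% power and the linear score about 60%.

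**Step 6: Bayesian reading.** With a weak prior, the ratio of the effect to its posterior SD shrinks by √E, to about 0.80 (p = 0.50) or 0.74 (p = 0.26) of its value with the score. That matches the 1.57 to 1.83 times in the table.

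**The case against.** The strongest reply is that no harm is shown. Section 3.6.1 says only that participants will be categorised; it names no test or model that uses the groups. The section 3.8 model keeps 12-month DASH as a score and leaves the form of the 3-month change open. If the groups are only descriptive, nothing is lost. This stands in part. A reader might infer that the primary model uses the two groups and so is underpowered, but the article does not say so. A loss there is a risk, not an established fact. What remains is that a grouping rule is fixed under the primary outcome heading and no other form of the variable is given, so this goes beyond detail left to an analysis plan.

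A second reply is that the cut was set in advance with a reason, and that +3 may be a real threshold. The first half is true and protects against a data-driven cut, but it does not restore the lost information. On the second half, a reader might infer that the cited cohort shows no step at 3 points. The article's one-sentence summary neither shows nor excludes a step, and the source is not at hand, so that argument is not used here.

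A third reply is that fixed-sample power at 0.05 fits a Bayesian, multi-covariate mixed model poorly. This is fair. The percentage-point figures are a yardstick, and covariate adjustment would change them. The loss of efficiency itself carries over, as less precise posteriors or more participants.

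**Conclusion.** The point holds in conditional form. Section 3.6.1 commits to a two-group version of the 3-month change that also counts decliners as maintainers, and section 3.8 does not say that the score will be used instead. Where the groups serve inference, and if the change is near normal with a roughly linear effect, at least about 36% of the information goes. The loss reaches about 45% at 26% improvers and rises further if fewer improve. From an assumed 80% power, that is about 19 to 25 points lost with 26% to 74% improvers.

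It would be too strong to say that every analysis using the groups loses 36% to 45%, or a flat 20 points. The first figure is a floor, the second is not a ceiling, the drop varies with the reference power and the share of improvers, and the groups do better if the effect is truly a step at +3.

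**What to change.** In sections 3.6.1 and 3.8, state that the baseline-to-3-month DASH change enters every inferential model as a score, whether as outcome or as explanatory variable, with baseline DASH in the model. Report results per 3-point difference, which keeps the cited benchmark, and include a check for curvature, which would also show whether a step near +3 is plausible. Keep the improver and maintainer groups for descriptive tables only.

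The cost is a change of wording and a little extra modelling on the same data. The study also gives up a simple two-group headline.

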## Abstract

Diet quality influences glycemic control in people with type 2 diabetes (T2D), impacting their risk of complications. While there are many cross-sectional studies of diet and diabetes, there is little understanding of the extent to which people with T2D change their diet after diagnosis and of the factors that impact those changes. This paper describes the rationale for and design of the 3D longitudinal Study which aims to: (i) describe diet quality changes in the 12 months following T2D diagnosis, (ii) identify the demographic, physical and psychosocial predictors of sustained improvements in diet quality and glycemic control, and (iii) identify associations between glycemic control and diet quality in the 12 months following diagnosis. This cohort study will recruit adults registered with the Australian National Diabetes Services Scheme who have been recently diagnosed with T2D. Participants will be involved in five purposefully developed telephone surveys, conducted at 3 monthly intervals over a 12-month period. Diet quality will be determined using a 24-h dietary recall at each data collection point and the data will be scored using the Dietary Approaches to Stop Hypertension (DASH) diet-quality tool. This study is the first dedicated to observing how people newly diagnosed with T2D change their diet quality over time and the predictors of sustained improvements in diet and glycemic control.

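### The improver label comes from the difference between two single-day recalls, so the 3-point cut mixes day-to-day variation with real dietary change

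*Protocol article*

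**What the plan says.** Section 3.6.1 states that "Change in DASH score from baseline to 3 months will be used to categorize participants as diet quality improvers or diet quality maintainers". Improvers are "those who improved their DASH score by at least 3 DASH points (Diet quality improvers". The other group takes in everyone else, including those who got worse: "maintained their DASH score within 2.99 points or decreased their DASH score by at least 3 points (Diet quality maintainers".

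The Abstract fixes the measurement: "Diet quality will be determined using a 24-h dietary recall at each data collection point". Section 3.6.1 describes a tool built around "remembering and reporting foods eaten in the previous 24 h". No repeat recall within a time point is described.

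On scoring, "The standard scoring tool determines a score between 8 and 40 points" and "For each of the components, participants are classified according to their intake ranking"; Table 3 lists eight components worth 1 to 5 points each. The 3-point cut is taken from a 20-year study of more than 40,000 adults, in which a change of about that size was related to long-term glycemic control.

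Section 3.8 makes the 12-month DASH score the primary outcome and lists interim diet changes, mainly those at 3 months, among the explanatory variables. It adds: "This model will determine the relative importance of diet quality change both immediately after diagnosis and in the medium term". The same section refers to a Bayesian mixed model that is updated as data arrive. The Discussion acknowledges dietary measurement error and relies on the validated tool to limit it. The article gives no SD for the score and no within-person variance.

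**The concern.** One recalled day describes that day, not usual diet. The difference between two such days carries the daily error twice. A cut calibrated on long-term change in a large cohort has no known meaning for a one-day difference whose noise may be as large as the cut or larger.

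Two consequences follow. First, selecting people on an observed rise favours a poor baseline day and a good 3-month day. Their later scores then move back toward their usual level whether or not their diet changed. The Discussion wants to learn why some people sustain change and others do not, so a trajectory plot of the improver group would be read on exactly that question. Second, the observed 3-month change is an error-laden explanatory variable for the 12-month score, so its coefficient does not estimate the importance of a real early change.

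**Working it through.** **Inputs.** From the article: cut of +3, one recall per time point, integer scores from 8 to 40 built from eight components scored 1-5. Not in the article, hence assumed: the SD and the single-day reliability (ICC). A quintile score has variance (25 − 1)/12 = 2, so eight independent components give SD √(8 × 2) = 4. A correlation of 0.1 between components raised this to 5.1 in simulation. Main range: SD 4-5, ICC 0.2-0.5. SD 3 and ICC 0.9 are shown as limits. The article has no figure of its own to reproduce.

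**Step 1: labelled improvers when nobody changes.** SD of the difference = SD × √(2(1 − ICC)). For integer scores, P(improver) = 1 − Φ(2.5 / SD of difference).

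| SD | ICC | SD of difference | P(improver) |
|---|---|---|---|
| 4 | 0.5 | 4.00 | 26.6% |
| 4 | 0.2 | 5.06 | 31.1% |
| 5 | 0.5 | 5.00 | 30.9% |
| 5 | 0.2 | 6.32 | 34.6% |
| 3 | 0.5 | 3.00 | 20.2% |
| 3 | 0.2 | 3.79 | 25.5% |
| 4 | 0.9 | 1.79 | 8.1% |
| 5 | 0.9 | 2.24 | 13.2% |

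Using 3 in place of 2.5 (no integer correction) gives 23-32% over the main range. A simulation of 200,000 people, with eight components cut into quintiles, gave 27.5-35.1% over the main range. It gave 12-16% at component ICC 0.9, where the summed score is slightly less reliable (correlation 0.85-0.87).

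**Step 2: what false improvers do next.** With equal error variance at both visits, half of a noise-only rise lies in the high 3-month day and half in the low baseline day. The expected later fall is therefore half the rise, and the other half remains as an apparent gain over baseline. In the simulation (SD 4-5.1, ICC 0.2-0.5):

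- rise at 3 months: 5.1-6.9 points
- fall from 3 to 12 months: 2.6-3.4 points, with 51-56% losing 3 points or more
- apparent gain from baseline to 12 months: 2.5-3.5 points
- rise among maintainers from 3 to 12 months: 1.0-1.9 points

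Example at SD 4, ICC 0.5: means of 21.5, 26.5 and 24.0 at 0, 3 and 12 months. The fall is 26.5 − 24.0 = 2.5 and the retained gain is 24.0 − 21.5 = 2.5.

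**Step 3: observed change as a predictor.** Let t be the variance of stable usual diet, e the daily error variance, and u the variance of a true early change that persists fully (true coefficient 1). Take u = 4 or 9 (SD 2-3), SD 4-5, ICC 0.3-0.5.

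- Without baseline DASH: u/(u + 2e). Lowest: SD 5, ICC 0.3, 4/(4 + 35) = 0.10. Highest: SD 4, ICC 0.5, 9/(9 + 16) = 0.36.
- With baseline DASH: [(t + u)(t + e) − t²] / [(t + e)(t + u + e) − t²]. Lowest: (11.5 × 25 − 56.25)/(25 × 29 − 56.25) = 231.25/668.75 = 0.35. Highest: (17 × 16 − 64)/(16 × 25 − 64) = 208/336 = 0.62.
- With baseline DASH and no true change (u = 0): ICC/(1 + ICC) = 0.23 to 0.33, where the right answer is 0.

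**Step 4: how well all five recalls recover one person's early change.** If the change persists through all four follow-ups and the variances are known, reliability = u(t + e) / [(t + e)(t + u + e/4) − t²]. At SD 5, ICC 0.3, u = 4 this is 100/340.6 = 0.29. At SD 4, ICC 0.5, u = 9 it is 144/240 = 0.60.

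**The case against.** The strongest reply is that the article describes no analysis following improvers from month 3, and does not say that the two-group label enters the regression. Its stated outcome is the 12-month score. With no true change, improvers and maintainers have the same expected 12-month mean (about 24 in the example), so that comparison shows no false difference unless baseline is adjusted for. Aim (i), the whole-cohort course, is not touched by the selection. This stands. It limits the point to trajectories of the selected groups and to the observed-change predictor.

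The article also acknowledges measurement error and cites evidence that the recall is valid at a given time point. It would be unfair to say that error is ignored. But a valid record of a day does not make that day usual diet, and no correction is described.

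Several stronger readings are tempting and not supported:

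- That about a third of people would be mislabelled. This is the upper part of a range built on an SD and ICC that the article does not give.
- That the study would confirm its own hypothesis of early improvement that fades. The aims state no such hypothesis; the Introduction reports that pattern only from earlier qualitative work.
- That the label manufactures relapse. Measured from baseline, the same selection looks like partial maintenance.
- That the importance of early change would always be understated. With baseline DASH in the model and no true change, it is overstated.
- That a person with a true gain of exactly 3 is caught only about half the time. That is so for any symmetric error around a cut and says little about this one.

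**Conclusion.** The point holds in limited form. The rule in Section 3.6.1 applies a long-term threshold to a difference between two single days, and the text shown does nothing to separate daily variation from change. Under the assumed SD of 4-5 and ICC of 0.2-0.5, roughly a quarter to a third of participants would be called improvers with no true change. Their later course is distorted by about 2.5-3.4 points, close to the study's own threshold. The share falls to 20-26% at SD 3 and to 8-13% at ICC 0.9.

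The coefficient of observed 3-month change on 12-month DASH is biased either way: 0.10-0.36 without baseline DASH and 0.35-0.62 with it when the truth is 1, and 0.23-0.33 with baseline when the truth is 0. All sizes rest on assumed variances. The direction of the selection effect does not; it needs only daily error in the two scores that define the groups.

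**What to change.** - Keep the improver/maintainer split for description only. Do not use it as an analysis variable, and do not interpret improver trajectories from the same scores that selected them.
- In the Bayesian mixed model already planned in Section 3.8, fit all five recalls with piecewise time (0-3 and 3-12 months) and person-level random change. Relate later diet and the candidate predictors to the estimated latent early change, carrying its uncertainty forward.
- State that individual classification remains imprecise with one recall per time point. The reliability of 0.29-0.60 in Step 4 is a favourable case, since it assumes a fully persistent change and known variances. A label based on posterior probability would not remove this limit.

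The change is to analysis wording; no further recalls are needed. The cost is a less simple two-group presentation and wider intervals. The article fixes no sample size, so how well the variance of early change can be estimated will depend on the number finally recruited.

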This paper describes the methodological protocol of the 3D Longitudinal Study, so named because seeing something in three dimensions adds clarity. In this case it refers to the 3D’s of Diet, after Diagnosis with Diabetes. The study aims are to: (i)Describe diet quality changes in the 12 months following T2D diagnosis. (ii)Identify the demographic, physical and psychosocial predictors of improvements in diet quality and glycemic control. (iii)Identify associations between glycemic control and diet quality in the 12 months following diagnosis.

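### DASH components are scored by participants' intake quintiles with no stated reference distribution; if quintiles are re-derived at each wave, mean change in diet quality cannot be seen

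*Protocol article*

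**What the plan says.** Section 3.6.1 of the protocol article sets out the scoring in some detail. On each component, "For each of the components, participants are classified according to their intake ranking". For the favourable components, "quintile 1 is assigned 1 point and quintile 5 is assigned 5 points". For sodium, red and processed meats, and added sugar the order is reversed: "The lowest quintile is given a score of 5 points and the highest quintile is given a score of 1 point". On the total, "The standard scoring tool determines a score between 8 and 40 points".

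Table 3 repeats the scheme with Q1 to Q5 labels, explained only as running from low to high consumption. It gives no servings or milligrams, and names no reference population or reference wave.

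The same score then carries three uses:

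- Aim (i) in the Introduction: "Describe diet quality changes in the 12 months following T2D diagnosis".
- The improver rule in 3.6.1: a gain of at least 3 points from baseline to 3 months.
- The modelled primary outcome in 3.8: the DASH score at 12 months.

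Section 3.4 fixes five waves (0, 3, 6, 9 and 12 months). Under 3.8 there is no preset sample size, and "the parameter estimates of the mixed model will be sequentially updated as batches of data are obtained".

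**The concern.** A quintile score is relative. It says where a person stands in some distribution, so it can show change over time only if that distribution is held still. The only distribution the scoring rule mentions is that of the participants themselves, and nothing says it is held still from wave to wave.

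Suppose each wave is ranked afresh. A cohort that improves together keeps the same ranks and shows no mean change. If only part of the cohort improves, those who ate the same as before fall in rank and appear to have worsened. The 3-point threshold, which the protocol justifies by its relation to long-term glycemic control, would then be applied to shifts in position rather than to dietary change. Aim (i) and the improver classification are the parts most exposed.

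**Working it through.** **Inputs from the protocol article.** Points 1 to 5 per quintile, five components scored upward and three in reverse (3.6.1, Table 3); score range 8 to 40 (3.6.1); improver threshold 3 points (3.6.1); five waves (3.4).

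**Step 1. Reproduce the stated range.** Eight components give 8 × 1 = 8 to 8 × 5 = 40, as stated. Seven would give 7 to 35. Section 3.6.1 counts seven components but names eight: its list ("summing the number of daily servings of seven dietary components; fruits, vegetables, nuts and legumes, whole-grains, low-fat dairy, red and processed meats, added sugar, and") closes with one more item, sodium. Table 3 also has eight rows, so eight is used here.

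**Step 2. Mean under re-ranking.** With equal quintiles and no ties, each component averages (1+2+3+4+5)/5 = 3, in either scoring direction. The total averages 8 × 3 = 24 at every re-ranked wave, so mean change is 24 − 24 = 0 for any common shift in diet.

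**Step 3. Mean under fixed baseline cut-points (illustrative).** Assume normal components and a gain of s SD on every component. The baseline quintile cut-points are c = −0.842, −0.253, 0.253 and 0.842. The expected component score at follow-up is 1 + Σ[1 − Φ(c − s)].

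- s = 0.25: 1 + 0.862 + 0.693 + 0.499 + 0.277 = 3.331. Times 8 gives 26.65, a change of about +2.7.
- s = 0.5: the same formula gives a change of 5.19, about +5.2.

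**Step 4. Effect on the 3-point rule.** Simulation with eight normal components, assumed within-person correlation 0.4, n = 1000:

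| True gain per component | Mean, re-ranked | Share gaining ≥3, re-ranked | Mean, fixed baseline cut-points | Share gaining ≥3, fixed |
|---|---|---|---|---|
| 0 | 24.0 | 29% | 24.0 | 29% |
| 0.25 SD | 24.0 | 29% | about 26.7 | 51% |
| 0.5 SD | 24.0 | 29% | 29.2 | 73% |
| 1.0 SD | 24.0 | 29% | 33.6 | 95% |

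Quintiles taken from the two waves pooled recover nearly the same changes (2.7, 5.2 and 10.0 points).

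**Step 5. Only half improve, by 0.5 SD.** Re-ranked, improvers show about +2.6 and unchanged people about −2.6, which sum to zero as they must. With fixed cut-points the figures are about +5.2 and 0.

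**Step 6. How firm is 24?** Two things move it.

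- Sample size not divisible by five: at n = 22 the rank rule used gives groups of 5, 4, 5, 4 and 4. A favourable component averages 64/22 = 2.909 and a reversed one 3.091, so the total is 5 × 2.909 + 3 × 3.091 = 23.82. This is slightly off 24 but still constant for that n.
- Ties at zero, plausible with one 24-hour recall per wave: if 50% report none of a component and ties go to the lowest group, its mean falls from 3 to about 2.6; at 70% it is about 2.1. A re-ranked mean can therefore move when the share of zeros changes.

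**The case against.** The strongest reply is that re-ranking at each wave is stated nowhere. The text is also compatible with quintiles from baseline, from pooled waves or from an external population, and under any of these the change is visible. The protocol relies on a cited standard tool, and a condensed article may leave the source of cut-points to a fuller document. Section 3.6.1 also reports that the feasibility data could be used to assess 12-month change.

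Most of this stands as a limit on the claim. A reader might infer that the study cannot detect dietary change at all; the documents do not support that. Even under re-ranking, change relative to peers survives, and so do between-person comparisons at 12 months, on which much of the model in 3.8 depends. The feasibility remark does not settle the matter, since it does not say how those scores were referenced and only 17 − 6 = 11 participants remained.

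Two further inferences should be resisted. The cited cohort's mean ("an average DASH score of 23.8 out of 40 was observed") is not evidence of within-sample ranking: the midpoint of an 8 to 40 scale is (8 + 40)/2 = 24, and the article does not say how that cohort was scored. Nor can one conclude that earlier posteriors are invalid priors for later batches. That would need scores to be re-ranked as batches arrive, which 3.8 does not say.

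What does not stand is the defence of mere brevity. The article states the scoring rule and a numeric threshold, the rule is relative, and the only distribution it names is the participants' own. That suits absolute change poorly unless it is anchored.

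**Conclusion.** The point holds conditionally. The protocol defines a rank-based score for a repeated-measures outcome and leaves the reference distribution open. Under one permitted reading, re-derivation at each wave, the mean is held at about 24, mean change under Aim (i) cannot be seen, and the improver share does not respond to a common improvement in diet.

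The zero mean change follows from the arithmetic, given near-equal quintiles and few ties; it does not depend on the assumed correlation. The +2.7 and +5.2 points, the 29% and the other shares are illustrations that rest on assumed normal components and uniform SD gains (the shares also on the assumed correlation of 0.4). They are not forecasts for this cohort. The choice should be settled before any change score is computed.

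**What to change.** State in 3.6.1 and Table 3 that one set of component cut-points is applied unchanged to all participants and all five waves, with no re-ranking by wave or by batch. Give an explicit rule for zero intakes, so that tied zeros always receive the same category.

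Preferably use absolute cut-points or cut-points from an external population, set before scoring begins. These suit the batch updating in 3.8 because they do not wait for the sample to fill. The article refers to the national nutrition survey only for recall methodology and gives no cut-points from it, so the source would have to be named.

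If baseline-sample quintiles are used instead, lock them before any follow-up change score is computed, and rescore earlier batches with the locked values before the final analysis. The baseline sample will be incomplete when the first updates are made, so those updates should be treated as provisional.

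Correct the count of seven components to eight at the same time.

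The cost is protocol wording and scoring syntax. The small downside is slightly less comparability with cohorts that used their own internal quintiles.
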